#### Early termination

We do not expect any complications to arise from use of the bundle. In the unlikely event that any do, the investigators will liaise with the patient’s primary clinicians to manage any such complications. Then, taking into account the nature of the event, the certainty of association with the study intervention and the likelihood of recurrence, consideration will be given to terminating the study. Every effort will be made to avoid early termination for any reason other than safety.

In the event of early termination of the study, the Australian and New Zealand College of Anaesthetists, Becton, Dickinson and Company, the ethics committee and the trials registry will be notified.

#### Process data

At present, funding limits the extent to which we can evaluate current practices and changes to these practices after the implementation of the bundle. However, a small sample of cases will be observed at each site before and after implementation of the bundle to assess aseptic practices of the anaesthetic team using a BARS as described under the “Process measures” subsection. As indicated above, all participating staff (anaesthetists, anaesthetic technicians, surgeons and operating room nurses) will be informed of this aspect of the study at its outset, and relevant information will be included in the presentations to the departments and online. Individual consents will not be obtained.

Depending on availability, our observations will be done by people who are able to spend time in the operating room without necessarily attracting attention (e.g. medical students, nurses, anaesthetists or anaesthetic technicians) and who will be independent of the study in all other respects. Observations will be done on a pragmatic basis at times determined by the availability of these observers. Before starting the collection of baseline study data, preliminary observational data will be obtained to refine the BARS and establish its key properties, such as usability, reliability and interobserver repeatability. Within the time periods in which such staff are available for the study, we will randomly allocate the departments and operating rooms to be observed on any particular day, with stratification to ensure coverage of all the departments at each period of observation. As the study progresses, we will thus obtain information about both control and active phases of the study over time.

These observers will be trained in the use of the study BARS by one of the investigators. Training will also reinforce operating room etiquette and the need for the observations to be done discretely. Entire cases will be observed, producing one complete BARS form (and score) per case.

### Timeline

The study is expected to run for 3 years from November 2018. We present a detailed schedule of enrolment, interventions and assessments as per the Standard Protocol Items: Recommendations for Interventional Trials (SPIRIT) guidelines (Fig. 2) [44]. The SPIRIT checklist is provided in Additional file 3.

**Fig. 2 Fig2:**
[figure not shown]
SPIRIT figure showing schedule of enrolment, interventions and assessments. Baseline data collection will be from 20 May 2018

## Discussion

Successful implementation of improvements in aseptic practices associated with anaesthesia has the potential to reduce postoperative infections. If this trial shows a positive change (i.e. an increase) in DAOH_90_ after implementation of our bundle, this will add to existing evidence suggesting that the practices of anaesthesia providers are a factor in the genesis of postoperative infections, and that improved outcomes can be achieved relatively easily. The investigators are well placed to liaise with relevant organisations to promote the subsequent adoption of the bundle throughout NZ. The potential benefits in relation to reducing patient harm and the costs associated with this are substantial, and the implications for Māori and Pacific patients may be particularly important.

Our bundle was designed to be simple and practicable. Some participants in our focus groups would have liked a more comprehensive bundle, aimed at perfect aseptic practice. In our view, more substantial changes in practice would be difficult to achieve, even in the context of a trial. Asking for too much may impede the readiness of participants to accept the bundle. It is also a strength that the evidence supporting our initiative is already known to many of our participants, in part because of previous studies undertaken on this topic in Auckland. In particular, the fact that the research into the potential role of the filters was both local and recent encourages us to believe that their potential value will be readily appreciated by participants.

One reason that the more general elements of the bundle have not already been more widely embraced may be the fact that infections that follow failures in aseptic practice manifest long after anaesthesia has finished. Thus, a postoperative infection is seldom, if ever, tracked back to the source, and there is no feedback to the anaesthetists about the consequences of such failures. In practice, it is quite difficult to achieve perfect aseptic practice during the dynamic and complex conduct of anaesthesia, and there are often more immediate threats to the patient. Greater motivation to maintain asepsis is required, and providing that motivation will be a key element of this initiative. Even with greater motivation, the required improvements in practice will need to be reasonably easy to implement, and as stated, we have strived to ensure that this applies.

What if our trial produces a negative result (i.e. no statistically significant change in DAOH_90_)? The question arises of how small a difference in DAOH_90_ actually matters? Might we miss a small difference that actually matters? The distribution of this variable is highly skewed and reflects the fact that most patients do not become infected and so will not experience any change in this outcome. We can expect the change, if it occurs, to be seen in the DAOH_90_ experienced by patients at lower centiles of the distribution. Thus, the difference may be more marked at the 25th percentile than at the 50th centile. With this in mind, our analysis will start by testing whether the distributions are significantly different or not (using a rank sum test tailored for a stepped wedge study that makes no assumptions about the nature of the distribution). If so, we will then provide numeric data on DAOH_90_ at the 10th, 25th, 50th, 75th and 90th centile and graphic representation of both distributions across the entire range to show where the effect lies. This approach avoids multiple testing and at the same time allows the maximum impact to be seen clearly without having to guess at the outset where it may lie (i.e. the 10th, the 25th or some other centile). We anticipate that this approach will mitigate the risk of missing clinically important differences between our groups.

We believe that DAOH_90_ may be a more powerful and more clinically relevant outcome measure for our study than the rate of infections per se. Nevertheless, we will utilize national databases to collect data on infections with a view to detecting any signal that will help attribute any differences in DAOH_90_ to differences in infection.

We believe the trial is well designed to test its primary hypothesis. The findings of this trial should add substantially to our understanding of postoperative infection. The trial is a direct response to the call by the World Health Assembly for new strategies “leading to strengthened infection prevention and control programmes, including… ...infection prevention practices in surgery” [5].

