### Statistics and sample size

DAOH_90_ data have a bimodal, left-skewed distribution that does not lend itself to parametric analysis. Data from a previous study of 20,000 general surgery procedures indicate that most patients score highly, so comparing measures of central tendency between groups can exclude the patients who are most likely to realise improved outcomes. Although our preference would be to use permutation testing methods, our five-cluster, five-sequence design only allows for 120 permutations. We consider this too low a number for a precise estimation of the significance of the difference between control and intervention cases. We will thus use a single Wilcoxon-Mann-Whitney *U* (WMWU) rank sum test as our omnibus test to ascertain whether intervention patients have significantly higher DAOH_90_ than control patients. This WMWU test will also be sensitive to prevailing trends in patient outcomes, so we will further investigate the difference using quantile regression. Models will be fitted at quantiles 0.1, 0.25, 0.5 and 0.75, with DAOH_90_ as the outcome, and time, intervention and site as the predictors. We will characterise any differences in distribution between groups by reporting differences associated with the intervention term in each model, and their significance.

We have used simulations to estimate our statistical power. Datasets were synthesised using distributions generated from four of our sites (excluding Starship Children’s Hospital) with different step lengths. Starship Children’s Hospital data were synthesised on the basis of the distribution from Auckland City Hospital’s cardiac unit. Distributions for each site were tweaked by increasing or decreasing the relative likelihood of higher DAOH scores until the desired magnitude of difference appeared at quantile 0.25. We found that a step length of 180 days (i.e. 6 months) would give us 100% power to detect a 2 DAOH difference at quantile 0.25 between groups using the WMWU and 77.7% power to detect an intervention effect using quantile regression (both two-tailed α < 0.05), with just over 10,000 patients. The intracluster correlation coefficient was measured as 0.02. Cluster sizes in the simulation depended on the ratio of caseloads between sites (see Table 2). Our study statistician has estimated that we will recruit 5492 cases in each group and will require 8454 filter units.

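### The Discussion says the primary-outcome analysis avoids multiple testing, but the Methods plan four unadjusted quantile tests, and the two sections describe different procedures

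*Protocol article*

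**What the plan says.** Methods, Statistics and sample size. The primary outcome, DAOH90, is first tested once, by Wilcoxon-Mann-Whitney (WMWU). The purpose is worded as a "rank sum test as our omnibus test to ascertain whether intervention patients have significantly higher"; the quantity meant is DAOH90 and the comparator is the control phase. The article then concedes a weakness of this choice, namely that the "test will also be sensitive to prevailing trends in patient outcomes, so we will further investigate the difference using quantile regression". The regressions themselves are set out in these terms: "Models will be fitted at quantiles 0.1, 0.25, 0.5 and 0.75". Their predictors are the intervention, the site and time. What the article promises from them is "reporting differences associated with the intervention term in each model, and their significance". No condition on the rank test, lead quantile or multiplicity adjustment is stated. On power, the article says of 180-day steps that they "would give us 100% power to detect a 2 DAOH difference at quantile 0.25 between groups using the WMWU". The figure given for the regressions is lower: "77.7% power to detect an intervention effect using quantile regression (both two-tailed α < 0.05), with just over 10,000 patients".

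Discussion. The analysis starts with a rank sum test described as adapted to the stepped wedge design. What follows depends on its result: "If so, we will then provide numeric data on DAOH_90_ at the 10th, 25th, 50th, 75th and 90th centile". Plots of the two distributions come under the same condition. The article concludes: "This approach avoids multiple testing and at the same time allows the maximum impact to be seen clearly". Neither quantile regression nor p-values at the centiles are mentioned there.

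**The concern.** The two sections set out different analyses of the same outcome, and the statistical property claimed in one is not a property of the other. Under the Methods, the reader will see one omnibus p-value and four quantile p-values, with nothing to say which of the four carries weight. The Discussion adds that the authors do not want to guess in advance at which centile the effect lies. Together these invite emphasis on whichever quantile falls below 0.05, while the text assures the reader that multiplicity is not an issue.

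The conflict over the gate matters as well. The adjusted models are the only planned step that accounts for time and site. Whether they appear after a non-significant rank test should not depend on which section an analyst follows.

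**Working it through.** **The plan's own figures.** The 100% and 77.7% powers come from simulations on site distributions and caseloads that the article does not show, so they cannot be reproduced. The 120 permutations in the same section equal 5! and are correct.

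**The two sections side by side.**

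| Item | Statistics and sample size | Discussion |
|---|---|---|
| Rank test | single WMWU, no site or time term described | rank sum test adapted to the stepped wedge |
| Follow-up | quantile regression adjusted for time and site | centile values and plots |
| Condition | none | only if the rank test is significant |
| Quantiles | 4 (0.1, 0.25, 0.5, 0.75) | 5 (the 90th is added) |
| Significance at quantiles | reported for each model | not mentioned; multiple testing said to be avoided |

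**Four quantile tests, ungated.** The level is two-sided 0.05, the only one stated and not split.
- Independent: 1 − 0.95⁴ = 0.185.
- Upper bound: 4 × 0.05 = 0.20.
- Correlated: for quantiles p < q the asymptotic correlation of the estimates is √[p(1−q)/(q(1−p))]. For 0.1 and 0.25 this is √(0.1 × 0.75/(0.25 × 0.9)) = 0.577; for 0.1 and 0.75 it is 0.192. A multivariate normal simulation with these correlations gives 0.159.

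**The same tests behind a valid 5% gate.** Assume a 5 × 6 wedge with equal cells. The correlation between the rank test and the adjusted test at quantile p is √[3p(1−p)] × k. Here k² is the share of treatment-indicator variation left after adjusting for site and step: 2.333/7.5, so k = 0.558. Under the global null the chance of passing the gate with at least one significant quantile is about 0.019. It cannot exceed 0.05.

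**The same tests behind the plain WMWU.** Assume N = 2 × 5492 = 10,984, so m = 10,984/30 = 366.1 per cell. Take the stated ICC of 0.02, equal cells, no time trend and a normal approximation.
- Sites contribute 5, 4, 3, 2 and 1 intervention steps out of 6. The centred site totals are 2, 1, 0, −1 and −2, with squared sum 10. The centred treatment sum of squares is 7.5.
- Variance inflation: 1 + 366.1 × 10 × (0.02/0.98)/7.5 = 10.96.
- True two-sided level: 2[1 − Φ(1.96/√10.96)] = 2[1 − Φ(0.592)] ≈ 0.55.
- Passing this gate with at least one significant quantile: about 0.089. At ICC 0.001 the gate's level is about 0.11 and the joint figure about 0.028.

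**Could a gate hide an adjusted effect?** With equal cells, intervention cells have mean step 4.67 and control cells 2.33, a gap of 2.33 steps. The standard error of the pooled difference is 2/√10,984 = 0.0191 SD. A trend of 1.96 × 0.0191/2.33 = 0.016 SD per step therefore moves the pooled z by 1.96. Without such a trend the gate costs almost nothing at the design alternative, because the stated WMWU power is 100%: the power to pass both stays at about 77.7%.

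**The case against.** The primary decision rests on one designated omnibus test, and the quantile models are there to describe where a difference lies. All four are pre-specified and all four are to be reported, so quiet selection is limited. Taken alone, the Discussion's procedure (one test, then descriptive centiles and plots) does avoid multiple testing. Multiplicity rules for supportive models are often left to a statistical analysis plan, which is not shown here.

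Most of this stands. It confines the problem to quantile-level claims. It does not remove it, because the article makes a positive statement about multiplicity that conflicts with its own Methods; this is not mere silence on detail.

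A reader might infer two stronger things. The first is that the adjusted result will be withheld if the rank test is null. The text permits that reading but does not state it: the condition in the Discussion covers centile values and plots, and the Methods give the regressions without any condition. The second is that the plan suffers uncontrolled error and a suppressed adjusted analysis at once. These mostly belong to opposite readings: ungated, nothing is hidden; gated by a valid test, error under the global null is at most 5%. Only a gate that ignores site and time could bring both, and the Discussion describes its rank test as adapted to the design. Even that invalid gate is not idle: it cuts about 16% to about 9%.

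**Conclusion.** The point holds as a contradiction between the two sections and a wrong statement about multiplicity. For the four quantile tests as written in the Methods, the chance of at least one false positive is about 16%, with 18.5% under independence and 20% as the limit. The 16% rests on asymptotic normal correlations between quantile estimates.

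The omnibus decision is a single test and is not affected by this count. A valid 5% gate would give control under the global null only; it would not protect each quantile claim once a difference exists somewhere. The plain WMWU could not serve as such a gate: its level is about 55% at ICC 0.02, assuming equal cells and no trend. If the rank test really is adapted to the wedge, that figure falls away, but the Methods must then say so. Suppression of the adjusted models by a secular trend is a risk only if the Discussion's condition is extended to them.

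**What to change.** State one procedure in both sections:
- Describe the rank test in the same way, including whether it accounts for site and time.
- Report the quantile models adjusted for site and time whatever the rank test shows, and delete the condition in the Discussion.
- Use one list of quantiles, with or without the 90th.
- Present the quantile effects as estimates with confidence intervals and no significance claims, or adjust their p-values for multiplicity. Naming quantile 0.25 as the lead is an option, since the simulated effect was set there. It is not essential, and it sits uneasily with the stated wish not to guess where the effect lies.
- Delete the claim that multiple testing is avoided.

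The cost is wording only, with no new data or patients. The small downside is that a gain at a single quantile becomes descriptive or faces a stricter threshold.

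### The rank sum omnibus test has little power for a gain confined to about the worst tenth of patients, so the Discussion should limit its claim that the effect's location need not be guessed

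*Protocol article*

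**What the plan says.** Under Statistics and sample size, the Protocol article rejects summary comparisons of location because "comparing measures of central tendency between groups can exclude the patients who are most likely to realise improved outcomes". It then states: "We will thus use a single Wilcoxon-Mann-Whitney *U* (WMWU) rank sum test as our omnibus test". Quantile regression at 0.1, 0.25, 0.5 and 0.75, with time, intervention and site as predictors, follows as further investigation. That section puts no condition on it.

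Power came from simulation: "Distributions for each site were tweaked by increasing or decreasing the relative likelihood of higher DAOH scores" until the intended difference appeared at quantile 0.25. The result was "100% power to detect a 2 DAOH difference at quantile 0.25 between groups using the WMWU", against 77.7% for quantile regression ("both two-tailed α < 0.05").

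The Discussion says where an effect should appear: "We can expect the change, if it occurs, to be seen in the DAOH_90_ experienced by patients at lower centiles of the distribution". It adds that most patients are not infected and so will not change. The analysis is to begin with a rank sum test of whether the distributions differ. Only if they do will centile values and plots of both distributions be given. This is said to avoid multiple testing, and it "allows the maximum impact to be seen clearly without having to guess at the outset where it may lie", with the 10th and 25th centiles as examples. The authors expect it to reduce the risk of missing clinically important differences. They define a negative trial as one without a statistically significant change in DAOH90.

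**The concern.** A rank sum test is not a general test of whether two distributions differ. Its power depends on theta = P(Y > X) + ½P(Y = X) moving away from ½, where Y is an intervention case and X a control case. A patient in the worst decile who gains many days but stays in that decile overtakes only other patients in it. The change in average rank is then small however many days are gained.

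The Discussion expects the benefit low in the distribution and names the 10th centile as one place it may lie. It then makes the display of centiles depend on this test. If the benefit were confined to roughly the worst tenth of patients, the omnibus test would usually be non-significant. Under the Discussion's rule the trial would be called negative and the centiles would not be shown. The point does not depend on site or time effects; it holds for independent, balanced patients.

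**Working it through.** **Inputs.** From Statistics and sample size: "Our study statistician has estimated that we will recruit 5492 cases in each group", so n = 5492 per group; two-sided 5%; an illustrative fall in surgical site infection from 1.4% to 0.8%; and the design effect of 2.0 that the protocol uses for infection. The article gives no numerical DAOH90 distribution. Where a shape is needed, three left-skewed shapes with a lump at zero are assumed (arthroplasty-like, cardiac-like, mixed). Clustering is ignored unless stated.

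**1. The plan's own figure.** Each assumed shape was tilted towards higher scores until quantile 0.25 rose by 2 days. Theta became 0.56 to 0.68, z = 11.5 to 32, and power 1.000 in all three. With a design effect of 2 the smallest z is 11.5/√2 = 8.1, so power is still about 100%. The stated figure is reproduced. The same tilt also raised the median by 0.9 to 1.2 days and the 75th centile by 0.5 to 0.8 days, so it is not an effect confined to the low tail.

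**2. Standard error under the null.** SE = √[(2n + 1)/(12n²)] = √[10985/(12 × 5492²)] = 0.00551.

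**3. Ceiling for a gain confined to the worst fraction f.** Suppose only the worst fraction f change, and they stay at or below the control f-quantile. Only comparisons of a low case with a low case are affected. These are a share f² of all pairs, and within them the probability can rise at most from ½ to 1. Hence theta − ½ ≤ f²/2 for any distribution. Power = Φ(z − 1.96) + Φ(−z − 1.96), with z = (f²/2)/0.00551.

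| f | f²/2 | maximum z | maximum power | power at half the maximum shift |
|---|---|---|---|---|
| 0.05 | 0.00125 | 0.23 | 5.6% | 5% |
| 0.10 | 0.00500 | 0.91 | 14.8% | 7% |
| 0.15 | 0.01125 | 2.04 | 53% | 17% |
| 0.20 | 0.02000 | 3.63 | 95% | 44% |
| 0.25 | 0.03125 | 5.67 | about 100% | 81% |

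With a design effect of 2, the ceiling at f = 0.10 has z = 0.91/√2 = 0.64 and power about 10%. On the assumed shapes, lifting every patient in the worst decile to the 10th centile value is a mean gain of 2.1 to 3.2 days over all patients, and power is still only about 15%.

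**4. Patients who leave the lowest decile.** The ceiling assumes that patients stay in the tail, but an averted infection may move them out. If a share m moves from the lowest decile (mean rank 0.05) to the general distribution (mean rank 0.50), theta rises by about 0.45m.
- m = 0.6% (1.4% to 0.8%): shift 0.0027, z = 0.49, power about 8%.
- m = 1%: z = 0.82, power about 13%.
- m = 2%: z = 1.63, power about 37%.
- m = 3%: z = 2.45, power about 68%.

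For m between 0.6% and 2%, allowing for the assumed shape, this is about 7% to 38%. Power of 80% needs roughly 3.1% to 3.5% of all patients to move. The 0.6% is illustrative only, because DAOH90 also reflects other infections and complications.

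**5. Gains around the 10th centile and up to the 25th (assumed shapes).** A 2 to 3 day gain centred on the 10th centile gives about 8% to 16% power on one assumed shape, and 11% to 21% on another when it tapers to zero at the 20th centile. For gains capped at the 25th centile value, power is 19% to 73% for 2 days, 52% to 98% for 5 days and 80% to 99% for 10 days.

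**The case against.** A reader might infer that the protocol promises a test that finds the effect wherever it lies, that the test is blind to lower-centile effects generally, and that it must be replaced. The documents do not support any of these.

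- The Discussion says that centiles and plots will show where an effect lies once the test is significant, and that the approach should reduce the risk of missing differences. It does not guarantee detection.
- The design target is quantile 0.25, and 100% power there is plausible. For gains reaching the 25th centile, power runs from low to about 100% depending on size. The ceiling is already 95% at the 20th centile. The rank sum test is also not equivalent to comparing medians: a median comparison has no signal for a gain confined below the 25th centile.
- The Methods already plan a quantile model at 0.1 with no stated condition, so the low tail is not unexamined.
- A single test on the maximum over the four quantiles is no clear improvement. When gains stay strictly below the 10th centile, all four quantiles are unchanged and that test has almost no power (about 5% to 8% in simulation). It does much better when the gain falls on the 10th centile itself. The protocol gives adjusted quantile regression 77.7% power at the design effect. If that refers to one coefficient at 1.96, a critical value near 2.46 would leave about 60%.

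All of this stands, and it confines the point to effects in about the worst 10% to 15% of patients. It does not remove the point. The Discussion names the 10th centile and conditions its display on a test with little power there. The ungated quantile model lies outside the omnibus test and is not mentioned in the Discussion's rule for a negative result.

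**Conclusion.** The concern holds in limited form. The Discussion credits its approach with not needing to guess the effect's location, and the omnibus test lacks that property in the lowest decile. For gains confined to the worst 10% its power is at most about 15% (about 6% for the worst 5%, 53% for the worst 15%). These ceilings need only the planned 5492 per group, two-sided 5% and independent patients, not a DAOH90 shape. With a valid variance, clustering would lower them further. The figures for patients leaving the lowest decile, for gains around the 10th centile and for gains capped at the 25th rest on assumed shapes.

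The stated 100% power is not wrong, but it answers a broader alternative. The Discussion's gate and the ungated quantile models in the Methods also need to be reconciled: if gated, a low-tail benefit may never be displayed; if ungated, the statement that multiple testing is avoided needs qualifying. This is worth correcting, but it is not a reason to abandon the WMWU test.

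**What to change.** 1. In the Discussion, limit the claim about location: the rank sum test detects shifts in average rank and has low power for effects confined to about the lowest decile.
2. Rerun the existing power simulation with gains confined to the lowest 10% and the lowest 25%, and state the WMWU power for each beside the 100%.
3. Remove the condition on the WMWU result. Report the site- and time-adjusted estimates at 0.1, 0.25, 0.5 and 0.75 with confidence intervals, and the plots of both distributions, in every case. The plots matter because a gain wholly below the 10th centile leaves the 0.1 quantile unchanged.
4. State that these quantile results are secondary, acknowledge their multiplicity, and qualify the statement that multiple testing is avoided.
5. State that a non-significant WMWU alone is not evidence of no benefit in the low tail.

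The cost is wording and one simulation rerun, with no new data. The downside is that low-tail findings carry only secondary weight. Replacing the WMWU by a maximum-over-quantiles test is optional: it gains power for effects at the chosen quantiles, gains none for effects strictly below the 10th centile, and may lose power at the design effect.
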